**Figure 2 fig2:**
[figure not shown]
iTBS treatment protocol. Group A: 600 pulses sham iTBS + 15 min rest + 600 pulses sham iTBS + 15 min rest + 600 pulses active iTBS; Group B: 600 pulses sham iTBS + 15 min rest + 600 pulses active iTBS + 15 min rest + 600 pulses active iTBS; Group C: 600 pulses active iTBS + 15 min rest + 600 pulses active iTBS + 15 min rest + 600 pulses active iTBS; Group D: 600 pulses sham iTBS + 15 min rest + 600 pulses sham iTBS + 15 min rest + 600 pulses sham iTBS.

Following daily iTBS intervention, each participant will undergo conventional occupational therapy and physical therapy for 1 h. The daily rehabilitation programs consist of exercises designed to promote voluntary motor recovery, including muscle stretching, passive and passive-assisted mobilization, progressive neuromuscular facilitation training, and task-oriented training. All exercises are performed by the same experienced therapists, who are unaware of the group allocation.

### Outcome measures

2.6.

The Fugl-Meyer Assessment of the Upper Extremity (FMA-UE) score from baseline (T0) to end of intervention (T1) is defined as the primary outcome. The FMA-UE is a standardized scale of upper limb motor impairment ranging from 0 to a maximum of 66 points (Fugl-Meyer et al., 1975; Chen Y. F. et al., 2022). Secondary outcomes are the Wolf Motor Function Test (WMFT), Grip Strength (GS), MAS, Modified Barthel Index (MBI), and Stroke Impact Scale (SIS). The WMFT consists of 15 tasks, each of which must be completed in at least 120 s, and the performance on each task is scored on a six-point scale (0–5) (Morris et al., 2001; Wolf et al., 2001). The GS is measured with a grip dynamometer. During the measurement, the patient’s shoulder joint is abducted to 90°, the elbow joint is flexed to 90°, and the forearm is placed on the table. The patient is instructed to hold the grip dynamometer as hard as possible (Bertrand et al., 2015). The grip dynamometer automatically records the highest value. A total of 3 measurements are taken with a 1-min rest interval between each measurement. The MAS is commonly used to assess spasticity. The MAS scores for the shoulder, elbow, wrist, and fingers of the affected upper extremity will be recorded. The MBI is used to assess the patient’s ability to perform activities of daily living (ADL), including 10 items out of 100 points (Ohura et al., 2017). The SIS is one of the commonly used scales to evaluate the quality of life of stroke patients, which consists of eight items, and each item has a full score of 100 points (Mulder and Nijland, 2016), and we will take the average score of the eight items as the outcome. Each participant will undergo the following clinical assessments pre-treatment (T0), post-treatment (T1), and at the 3-weeks follow-up (T2): FMA-UE, MBI, SIS. The following clinical assessments will be performed only before and after treatment: WMFT, GS, MAS. We will also perform exploratory analyses based on the rs-fMRI data collected before and after the treatment.

The magnetic resonance imaging (MRI) data will be collected by using a Philips Ingenia 3.0 T Magnetic Resonance System at the China Rehabilitation Research Center. Three rs-fMRI sessions of 8 min 6 s each are acquired using a gradient echo planar imaging sequence with the following parameters: TR = 2,000 ms, TE = 30 ms, FOV = 224 × 224 mm^2^, Flip angle = 90°, matrix = 64 × 64, Slice number = 32, voxel size = 3.5 × 3.5 × 4.35 mm^3^. Anatomical images are acquired using a high-resolution T1-weighted sequence (TR = 7.13 ms, TE = 3.22 ms, Flip angle = 7°, 192 slices, FOV = 256 × 256 mm^2^, Matrix = 256 × 256, voxel size = 1 × 1 × 1 mm^3^).

### Data analysis

2.7.

We will use SPSS version 25 for statistical analysis. Analysis of variance (continuous and ordinal data) or χ^2^ tests (categorical data) will be used to compare demographic and baseline characteristics. A mixed-design ANOVA (between-subjects factor: group; within-subjects factor: time; and time-by-group interaction) will be used to detect any significant differences in the change of outcomes. Any factor with a significant difference between the groups at the baseline will be included as a covariate in the ANOVAs. If a significant time-by-group interaction effect is found, comparisons using pairwise *t*-tests will be performed by separately comparing the changes from baseline. Bonferroni correction is applied for *post hoc* tests. Before entering the data into the ANOVAs, the Shapiro–Wilk test will be used to test whether the data are normally distributed. For non-normally distributed measures, the non-parametric Kruskal-Wallis H test is performed to compare across conditions. The level of significance is defined as *p* < 0.05 (2-tailed). For missing data, intention-to-treat (ITT) analysis is used (Matilde Sanchez and Chen, 2006).

The pre-processing of the MRI data will be in accordance with the previously described pipeline (Yeo et al., 2011). After preprocessing, regional homogeneity (ReHo), degree centrality (DC), amplitude of low frequency fluctuations (ALFF), and seed-to-voxel analyses will be performed to measure functional connectivity within motor networks. ReHo is calculated based on the Kendall’s concordance coefficient, which is used to measure the time-series synchronization between a given voxel and neighboring voxels, with higher values representing better concordance between the local voxel and the regional brain activities. In network analysis, DC is the most direct measure of node centrality. A higher degree of a node means that the node has a higher DC and the node is more important in the network. The ALFF value is related to the strength of local neural activity. It is often used to measure the BOLD signal in the frequency range of 0.01–0.1 Hz (Zang et al., 2004). Differences between conditions are considered significant if *p* < 0.05 at the voxel level. A false discovery rate (FDR) cluster corrected *p* < 0.05 is applied.

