### Sample size

2.3.

According to a previously published meta-analysis comparing iTBS and sham stimulation (Zhang et al., 2017), the expected effect size Cohen’s d for the comparison of the two groups was 0.6, and the effect size (f) for the comparison of the corresponding four groups was approximately 0.3. Using G*Power v3.1.9.2, the estimated sample size required for a 4-group design with a ratio of 1:1:1:1, given a power of 0.95 and a 2-tailed alpha error probability of 0.05, is 44 patients in total. Considering a dropout rate of 20%, at least 14 participants are needed for each group. Therefore, 56 patients will be enrolled in this study.

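### The primary outcome is FMA-UE from T0 to T1, but the only specified test is a time-by-group interaction not limited to those two visits, and it gates the T0–T1 comparison

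*Protocol article*

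**What the plan says.** All references are to the protocol article.

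- **Endpoint (Outcome measures, 2.6).** The FMA-UE "score from baseline (T0) to end of intervention (T1) is defined as the primary outcome".
- **Visits (2.6).** Three scales are assessed at three visits: "pre-treatment (T0), post-treatment (T1), and at the 3-weeks follow-up (T2): FMA-UE, MBI, SIS". WMFT, GS and MAS are assessed only before and after treatment.
- **Test (Data analysis, 2.7).** One model serves all outcomes: "A mixed-design ANOVA (between-subjects factor: group; within-subjects factor: time; and time-by-group interaction) will be used to detect any significant differences" in the change of outcomes. The section does not say which visits make up the time factor for FMA-UE.
- **Next step (2.7).** "If a significant time-by-group interaction effect is found, comparisons using pairwise *t*-tests will be performed by separately comparing the changes from baseline". Then: "Bonferroni correction is applied for *post hoc* tests". The size of the Bonferroni family is not given.
- **Sample size (2.3).** "the effect size (f) for the comparison of the corresponding four groups was approximately 0.3"; the number required, "given a power of 0.95 and a 2-tailed alpha error probability of 0.05, is 44 patients in total". Neither the number of measurements nor the correlation between them is stated.

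No sentence says whether the interaction or the T0–T1 contrast decides the primary result.

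**The concern.** An endpoint that stops at T1 needs a test that stops at T1. If the interaction runs over T0, T1 and T2, it responds to any difference in the shape of the three-visit profile, including one that appears only after treatment has ended. Because the comparisons of change depend on it, T2 data then decide whether the primary contrast is examined at all.

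This can go wrong in two ways. The omnibus p-value can be significant with no difference at the end of treatment. Conversely, a real T1 difference that fades by T2 can be left untested because the gate did not open. The trial's stated conclusion concerns the dose response at the end of treatment, so the test that carries it should be fixed without ambiguity.

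**Working it through.** **1. What the interaction tests.** With k = 4 groups and m visits, the interaction has (k − 1)(m − 1) degrees of freedom.

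- m = 3 (T0, T1, T2): 3 × 2 = 6. This mixes the T0–T1, T0–T2 and T1–T2 changes.
- m = 2 (T0, T1): 3 × 1 = 3. This is exactly the one-way comparison of T0–T1 change, which is the stated endpoint.

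**2. Does the sample size show which was meant?** Taken from section 2.3: f = 0.3, alpha = 0.05, power 0.95, four equal groups. Assumed, because not given: the correlation ρ, and sphericity of 1. For the within-between interaction, λ = f²·N·m/(1 − ρ), df1 = (k − 1)(m − 1) and df2 = (N − k)(m − 1).

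| m | ρ | N | λ | df1, df2 | Power |
|---|---|---|---|---|---|
| 3 | 0.5 | 44 | 0.09 × 44 × 3/0.5 = 23.76 | 6, 80 | 96.1% (N = 40: 93.8%) |
| 2 | 0.6 | 44 | 0.09 × 44 × 2/0.4 = 19.80 | 3, 40 | 95.8% (N = 40: 93.6%) |
| 2 | 0.5 | 44 | 0.09 × 44 × 2/0.5 = 15.84 | 3, 40 | 90.4% |
| 2 | 0.5 | 52 | 0.09 × 52 × 2/0.5 = 18.72 | 3, 48 | 95.1% |
| 2 | 0.5 | 56 | 0.09 × 56 × 2/0.5 = 20.16 | 3, 52 | 96.5% |

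Dropout: 11/(1 − 0.2) = 13.75, so 14 per group and 56 in total, as stated. The figure of 44 is reproduced by three visits at ρ = 0.5 and also by two visits at ρ = 0.6, so it does not settle the question.

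**3. How the gate behaves on the three-visit reading.** Simulated trials with 11 per group, normal data, SD 1 at each visit and equal correlation between visits. Effects across the four groups are 0/0/0.6/0.6 SD. All of these settings are assumptions. Results move by about one percentage point between runs of several thousand trials.

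| Scenario | Quantity | ρ = 0.5 | ρ = 0.8 |
|---|---|---|---|
| Effect at T2 only | three-visit interaction significant | 33% | 75% |
| | T0–T1 test significant | 5% | 5% |
| | gate opens and a T0–T1 pair is then significant (Bonferroni, 6 pairs) | about 3% | about 4% |
| 0.6 SD at T1, 0.3 SD at T2 | three-visit interaction significant | 24% | 59% |
| | T0–T1 test significant | 32% | 70% |
| | T0–T1 test significant, gate shut | 11–13% | 11–13% |
| Same effect at T1 and T2 | three-visit interaction | 33% | 74% |
| | T0–T1 change | 32% | 71% |
| | T1 adjusted for T0 (ANCOVA) | 41% | 74% |

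With 14 per group, the T2-only rates for the gate are 43% and 86%. With no effect at any visit, the interaction and the T0–T1 test both stay near 5%.

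The powers in step 3 are not comparable with the 95% in step 2. In the formula, f measures the interaction deviations. A 0/0/0.6/0.6 effect at T1 alone gives group deviations of 0 at T0 and ±0.3 at T1. The interaction deviations are then ±0.15, so f is 0.15 rather than 0.3. Step 3 is for comparing tests with one another.

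**The case against.** The strongest reply is that section 2.7 is a generic sentence covering outcomes with two visits as well as three. It never says three visits for FMA-UE, and on a T0-and-T1 reading the interaction is the right test. It can be added that an article leaves such detail to the full plan. The first part is correct: three visits is an inference from the schedule. It is nevertheless the natural one, since FMA-UE has three visits and nothing restricts the factor. Nor is this only missing detail, because the article sets out a decision procedure, and as written that procedure does not match the endpoint.

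Three stronger readings are tempting, and the document does not support them.

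- **That a T2-only effect would be declared the primary result.** No text says so. Section 2.6 ties the primary outcome to T1, and the post hoc step compares changes from baseline separately with Bonferroni correction, so such an effect would appear as a T2 change. Carried through that step, a false T0–T1 finding arises in only about 3% to 4% of the simulated trials. The 33% to 75% would matter as a false primary claim only if the bare interaction p-value were reported as the result, which the text neither states nor excludes.
- **That N = 44 proves a three-visit test.** It fits three visits at ρ = 0.5, but two visits at ρ = 0.6 give the same number.
- **That a missing T2 would remove a patient with complete primary data.** Section 2.7 says only that intention-to-treat analysis is used for missing data; it states no exclusion.

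The post hoc step does not cure the other fault. When the gate stays shut, the T0–T1 comparison is not made.

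**Conclusion.** The concern holds as a mismatch between endpoint and test. The primary outcome ends at T1; the only specified test has a time factor not limited to T0 and T1, it gates the T0–T1 comparison, and nothing makes that comparison decisive. On the three-visit reading, the gate opens in about 33% to 75% of trials with a T2-only effect, and stays shut in about 11% to 13% of trials with a significant T0–T1 test when the T1 effect halves by T2. These sizes rest on 11 completers per group, an assumed correlation of 0.5 to 0.8, and an assumed 0.6 SD pattern. The mismatch in the text does not depend on them. It should be corrected before analysis, and the correction is easy.

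**What to change.** In Data analysis:

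- Name the group effect on FMA-UE at T1, adjusted for T0 (ANCOVA), as the single primary test at two-sided 0.05, not conditional on any interaction that includes T2.
- Follow it with Bonferroni-corrected pairwise dose comparisons at T1, and state the number of comparisons in the family.
- Make T2 a named secondary contrast.

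In Sample size, state the number of measurements and the correlation behind N = 44, and restate the power for the T0–T1 test.

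The cost is analysis wording and possibly a less favourable stated power. If ρ = 0.5 was used, a two-visit test has 90.4% power at 44 and 96.5% if all 56 complete. Holding 95% among completers would need 52, or 13 per group; 13/0.8 = 16.25, so 17 per group and 68 enrolled. If the calculation used two visits at ρ = 0.6, 44 stands. Those figures are for unadjusted change. In the sustained-effect simulations, baseline adjustment recovered the power: 41% and 74% for ANCOVA at T1, against 33% and 74% for the three-visit interaction.

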#### Inclusion criteria

2.2.1.

Participants are considered eligible if they meet the following criteria: (1) have a unilateral ischemic or hemorrhagic subcortical stroke; (2) first or previous stroke without residual disability (modified Rankin Scale ≤1 before this onset); (3) 1–6 months post-stroke; (4) are 35–75 years old; (5) presented with a unilateral upper limb motor dysfunction with a Brunnstrom stage score between 2 and 5 in the upper limb or hand; (6) can sign an informed consent form.

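### Covariates are chosen by baseline significance tests, so the primary model is not fixed in advance and precision from regression on baseline FMA-UE is usually given up

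*Protocol article*

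**What the plan says.** Section 2.7 (Data analysis) of the protocol article says that ANOVA or χ² tests "will be used to compare demographic and baseline characteristics". The outcome model is "A mixed-design ANOVA (between-subjects factor: group; within-subjects factor: time; and time-by-group interaction"), and the covariate rule follows: "Any factor with a significant difference between the groups at the baseline will be included as a covariate in the ANOVAs". If the interaction is significant, "comparisons using pairwise *t*-tests will be performed by separately comparing the changes from baseline", with Bonferroni correction; no covariate is named for these. The level is fixed by "The level of significance is defined as *p* < 0.05 (2-tailed").

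Section 2.6 (Outcome measures) says that the FMA-UE "score from baseline (T0) to end of intervention (T1) is defined as the primary outcome", and schedules assessments at "pre-treatment (T0), post-treatment (T1), and at the 3-weeks follow-up (T2): FMA-UE, MBI, SIS". Section 2.4 describes block randomisation and mentions no stratification. Section 2.2.1 admits patients 1 to 6 months after stroke who "presented with a unilateral upper limb motor dysfunction with a Brunnstrom stage score between 2 and 5" in the upper limb or hand.

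**The concern.** In a randomised trial, baseline differences between groups arise by chance. A test of such a difference does not show whether a variable deserves adjustment; that depends on how strongly it predicts the outcome. Under the stated rule a strong predictor and an irrelevant one have the same chance of entering, about 5% each.

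Two things are at stake. The primary model cannot be written down before baseline data are seen. And the precision available from regressing on baseline FMA-UE, which every patient has at T0, is normally given up, in a trial with 14 patients per group before dropout.

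The rule also fits the chosen model badly. If baseline FMA-UE is selected, it is both the T0 response and a covariate in one repeated-measures ANOVA. The follow-up t-tests on change, which carry the dose comparisons, would still have no covariate.

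**Working it through.** **Inputs from the protocol.** Four groups, 1:1:1:1; d = 0.6 for two groups and f = 0.3 for four; power 0.95; two-sided α = 0.05; 44 patients, or 56 after 20% dropout (all section 2.3). FMA-UE at T0, T1 and T2 (section 2.6).

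**Assumptions, because the protocol gives no figure.** Baseline–T1 correlation ρ from 0.5 to 0.9; equal SD at T0 and T1; 8 to 15 baseline factors tested.

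**1. The plan's own figure.** For a repeated-measures within–between interaction, λ = f²·N·m/(1 − ρ), with degrees of freedom (k − 1)(m − 1) and (N − k)(m − 1). With k = 4, m = 3 time points and ρ = 0.5 assumed, N = 44 gives λ = 0.09 × 44 × 3/0.5 = 23.76 and power 0.961. So 44 is reproduced. Per group, 11/0.8 = 13.75, rounded up to 14, hence 56.

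**2. How often the rule selects a factor.** Each factor enters with probability 0.05. In simulation (100,000 trials per scenario) the baseline FMA-UE test was significant in 4.9% to 5.1% of trials. With 56 patients the critical F(3, 52) is 2.78, so the observed f must exceed √(3 × 2.78/52) = 0.40.

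For at least one factor entering by luck:
- independent factors: 1 − 0.95⁸ = 34% and 1 − 0.95¹⁵ = 54%;
- factors correlated at 0.5 (simulated, 14 per group): about 26% for 8 and 37–38% for 15;
- factors correlated at 0.7: about 20–21% and 27%.

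**3. What the change score leaves behind.** For T0 and T1, the time-by-group test is a one-way ANOVA of change. If two groups differ by Δ at baseline, the expected T1 difference due to that imbalance is ρΔ, while the change score subtracts all of Δ. The remainder is (1 − ρ)Δ in the opposite direction. For Δ = 0.6 SD this is 0.30 SD at ρ = 0.5, 0.12 at 0.8 and 0.06 at 0.9.

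**4. Precision.** The residual variance is 2(1 − ρ) for change and 1 − ρ² for ANCOVA. Their ratio is (1 + ρ)/2: 0.75, 0.85, 0.90 and 0.95 at ρ = 0.5, 0.7, 0.8 and 0.9.

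**5. Power.** Take f = 0.3 on the T1 score and no true difference at T0. Then λ = 0.09N/[2(1 − ρ)] for change, on (3, N − 4) df, and λ = 0.09N/(1 − ρ²) for ANCOVA, on (3, N − 5) df. At N = 44 and ρ = 0.5, λ is 3.96/1 = 3.96 against 3.96/0.75 = 5.28.

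| ρ | N = 44: change | N = 44: ANCOVA | N = 56: change | N = 56: ANCOVA |
|---|---|---|---|---|
| 0.5 | 0.325 | 0.423 | 0.414 | 0.535 |
| 0.7 | 0.517 | 0.591 | 0.641 | 0.719 |
| 0.8 | 0.710 | 0.759 | 0.829 | 0.870 |
| 0.9 | 0.958 | 0.967 | 0.990 | 0.992 |

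The absolute levels are not comparable with the 0.961 in step 1. There, f = 0.3 is the size of the interaction itself, spread over the time points; here it is the separation of groups at T1. The comparison within each row is what matters.

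**6. The rule itself, simulated.** With 14 per group and f = 0.3, applying the protocol's rule to baseline FMA-UE gave power 0.42, 0.64, 0.83 and 0.99 at ρ = 0.5, 0.7, 0.8 and 0.9. ANCOVA in every trial gave 0.53, 0.71, 0.86 and 0.99. The loss is about 11, 7, 3 and 0 points. Under the null, the rule's type I error was 0.044 to 0.050. With an effect present, change-score ANOVA and ANCOVA disagreed on significance in about 1% to 20% of trials.

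**The case against.** The strongest reply is that baseline FMA-UE is not left to chance. The outcome runs from T0 to T1, T0 is a level of the time factor, and the follow-up tests use change from baseline. A reader might infer that an FMA-UE imbalance of, say, 0.6 SD goes uncorrected unless the baseline test detects it. The documents do not support that: the level is always subtracted, and only the (1 − ρ) remainder in step 3 stays. This part of the objection stands. For factors not built into the outcome, such as time since stroke, nothing is subtracted.

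Second, a data-dependent model may suggest inflated false positives. It should not. The rule is mechanical, stated in advance and uses baseline data only, and section 2.4 says that statisticians are blinded. The simulation shows no inflation. This stands too.

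Third, the gain may be small. The wide Brunnstrom range suggests a wide spread in baseline scores, which, other things equal, raises ρ, and at ρ = 0.9 the gain is one point or less. That is fair: the size is uncertain. But a high ρ is no reason to keep the rule, since fixed adjustment costs one degree of freedom and in the table never falls below the change score.

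Finally, one could leave covariates to a statistical analysis plan. But the article states a rule rather than omitting one, and a later plan could only repeat or contradict it.

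**Conclusion.** The point holds in limited form. Section 2.7 selects covariates by a criterion unrelated to their prognostic value, and nothing else in the protocol fixes them. The final model is therefore unknown until baseline data are seen, and regression on baseline FMA-UE is omitted in about 95% of trials.

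The cost is precision and some residual imbalance, not validity of the test. On the calculation at N = 44 it is about 10 points of power at ρ = 0.5, 5 at 0.8 and 1 at 0.9. The chance of at least one lucky covariate is 34–54% for 8 to 15 independent factors, or about 20–38% if they are correlated at 0.5 to 0.7. The correlation ρ, the number of factors and their correlations are assumptions. Confidence is high that the rule is poor, and moderate on how much it costs. The change is worth making before the analysis.

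**What to change.** Delete the selection rule in 2.7. Prespecify the baseline value of the outcome as a fixed covariate for FMA-UE and the other continuous outcomes, whatever the baseline tests show. For FMA-UE this means an ANCOVA of the T1 score on group and baseline FMA-UE, with the Bonferroni-corrected pairwise dose comparisons taken from that same model instead of from separate t-tests on change. Any further covariate, such as time since stroke, is the sponsor's choice but should be named now. Baseline tests, if still reported, should have no role in choosing the model. The ordinal MAS needs its own statement.

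**Cost.** No new data: the outcomes are already measured at T0 (Table 1), and time since stroke is known from eligibility. One degree of freedom is used. It is more than a one-sentence edit: the model and post hoc wording in 2.7 change, and 2.3 must be restated, because 44 is reproduced as a three-time-point interaction and not as an ANCOVA at T1. The restated calculation should give its assumed ρ and say what f refers to. With f = 0.3 read as the T1 separation, the table shows 44 patients reaching 0.95 power only at ρ = 0.9.

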One of the most important factors influencing the effectiveness of iTBS is the stimulus dose (Volz et al., 2013; Chung et al., 2016). When studying stroke patients, most researcher used a block of 600 iTBS pulses (Ackerley et al., 2014, 2016; Watanabe et al., 2018; Chen et al., 2019; Ding et al., 2021) and a few used two blocks of 600 pulses iTBS (Hsu et al., 2013; Chen et al., 2021). Previous studies in healthy human subjects suggested that iTBS might dose-dependently modulate neural plasticity, i.e., the higher the dose of iTBS, the greater the changes in neural plasticity induced (Nettekoven et al., 2014; Yu et al., 2020). Nettekoven et al. (2014) applied three blocks of 600 pulses iTBS to motor cortex and found that the cortical excitability enhancement effect was significantly greater than two blocks of 600 pulses iTBS and one block of 600 pulses iTBS. They also found that functional connectivity between M1 and ipsilateral dorsal premotor cortex continued to increase in a dose-dependent manner after 1,800 pulses of iTBS over M1. However, studies in healthy human subjects are insufficient to support the clinical application of iTBS. Other studies revealed that in patients with neurological disorders, high doses of rTMS produced stronger and longer lasting therapeutic responses than low doses (Nyffeler et al., 2009; Williams et al., 2018), but an agreement on how to select the best dose of iTBS for stroke patients with upper limb motor dysfunction is limited until now. There is a lack of studies comparing the difference in efficacy of different doses of iTBS for upper limb motor dysfunction in stroke patients.

Therefore, the objectives of this randomized controlled clinical trial are: (1) to investigate the safety and efficacy of one block of iTBS (600 pulses-iTBS), two blocks of iTBS (1,200 pulses-iTBS), or three blocks of iTBS (1,800 pulses-iTBS) in the treatment of upper limb motor dysfunction in stroke patients; (2) to compare the efficacy of three doses of iTBS; (3) to explore the neural mechanism of upper limb motor recovery after stroke using resting-state functional magnetic resonance imaging (rs-fMRI). Our hypothesis is that the higher the dose of iTBS, the greater the improvement in upper limb motor function in stroke patients. This study may provide new insights into the efficacy and underlying neuroplastic mechanisms of iTBS for treating poststroke upper limb motor dysfunction.

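### The time-by-group ANOVA is adjusted for baseline imbalance, but the dose comparisons that follow it are specified as t-tests on change, which carry no covariate

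*Protocol article*

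**What the plan says.** Section 2.7 (Data analysis) of the protocol article sets out a sequence.

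- Main test: "A mixed-design ANOVA (between-subjects factor: group; within-subjects factor: time; and time-by-group interaction) will be used to detect any significant differences in the change of outcomes".
- Covariates: "Any factor with a significant difference between the groups at the baseline will be included as a covariate in the ANOVAs".
- Follow-up: "If a significant time-by-group interaction effect is found", then "comparisons using pairwise *t*-tests will be performed by separately comparing the changes from baseline".
- Multiplicity: "Bonferroni correction is applied for" the post hoc tests. The number of pairs is not given.

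The Introduction makes it an objective to study the efficacy of each dose, and a second objective "to compare the efficacy of three doses of iTBS". The interaction test can only show that some arm changes differently from some other. Which dose differs from sham, and which from another dose, is decided in the follow-up step.

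**The concern.** The covariate rule is written for the ANOVAs. The next step names a different method, a t-test on change scores, and describes the comparisons as made separately. No sentence carries the covariates forward. The plan therefore adjusts the test that opens the way to the dose comparisons, but not the comparisons themselves.

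This matters only when the rule is triggered, that is, when some factor differs between arms at p < 0.05. If that factor also predicts recovery, part of a reported dose difference reflects the imbalance, although the adjusted ANOVA suggests that it has been dealt with. The interaction test and the pairwise results may then point in different directions.

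**Working it through.** **Inputs from the documents.** Section 2.3 (Sample size) gives four arms at 1:1:1:1, d = 0.6 for two groups, f = 0.3 for four, 20% dropout and 56 patients: "given a power of 0.95 and a 2-tailed alpha error probability of 0.05, is 44 patients in total".

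**Reproducing the plan's own figure.** A repeated-measures within-between interaction with k = 4 groups, and m = 3 times and correlation ρ = 0.5 (both assumed), has λ = f²Nm/(1 − ρ) = 0.09 × 44 × 3/0.5 = 23.76 on (k − 1)(m − 1) = 6 and (N − k)(m − 1) = 80 degrees of freedom. Power is 0.961 at N = 44 and 0.938 at N = 40, so 44 is reproduced. Then 11/0.8 = 13.75, rounded up to 14 per arm, or 56. The arms to consider therefore have 14 patients, or 11 after the planned dropout.

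**Assumptions.** The documents do not give the correlation r between an unbalanced factor and the change score; 0.3 to 0.5 is used. All six pairs are assumed to be tested, at 0.05/6 = 0.0083.

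**Model.** Factor x has SD 1, and change is y = r·x + √(1 − r²)·e, also with SD 1. For arms i and j:

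- Unadjusted contrast: ȳᵢ − ȳⱼ. Given the factor, its expectation is the true difference plus r(x̄ᵢ − x̄ⱼ).
- Adjusted contrast: (ȳᵢ − ȳⱼ) − b(x̄ᵢ − x̄ⱼ), where b is the pooled within-arm slope. The imbalance term is removed.

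200,000 trials were simulated per setting, keeping the roughly 5% (about 10,000) in which x differed between arms at p < 0.05. The interaction test was represented by the covariate-adjusted group test on one change score. That equals the time-by-group test with two visits; FMA-UE has three, so this is a simplification.

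**Shift in triggered trials, for the pair with the largest gap in x (r × gap):**

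| n per arm | Mean largest gap | r = 0.3 | r = 0.5 |
|---|---|---|---|
| 14 | 1.05 SD | 0.32 SD | 0.53 SD |
| 11 | 1.18 SD | 0.35 SD | 0.59 SD |

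For a pair not chosen by its gap (C versus D, n = 14, r = 0.5), the root mean square error is 0.47 SD unadjusted and 0.34 SD adjusted.

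**False positives in triggered trials, n = 14, requiring a significant interaction and applying Bonferroni (unadjusted / adjusted):**

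| Truth | r = 0.3 | r = 0.5 |
|---|---|---|
| All arms equal, any of six pairs | 2.8% / 3.8% | 2.7% / 3.5% |
| One arm differs by 0.6 SD, pairs among the three equal arms | 3.0% / 2.3% | 4.7% / 2.0% |
| One arm differs by 1.2 SD, same pairs | 3.8% / 2.2% | 7.2% / 2.4% |

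**If the factor is the baseline score itself.** Taking change removes its additive part and leaves regression to the mean, with slope −(1 − r₀₁) at equal variances, where r₀₁ is the T0–T1 correlation. At an illustrative r₀₁ = 0.8 the slope is −0.2, so a gap of 1.05 SD shifts the contrast by 0.2 × 1.05 = 0.21 SD of the score. The SD of change is then √(2 × 0.2) = 0.63 of the score SD, so this is 0.33 SD of change.

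**How often the rule triggers.** It triggers in 5% of trials per factor. With 5 to 10 independent factors (assumed), at least one triggers in 1 − 0.95⁵ = 23% to 1 − 0.95¹⁰ = 40% of trials.

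**The case against.** The strongest reply is that the text never calls the follow-up unadjusted. The comparisons come after the ANOVAs that hold the covariates, contrasts of adjusted means are themselves t statistics, and a condensed article may leave the mechanics to an analysis plan. Adjusted contrasts may have been intended. What stands of this is that the mismatch is inferred from the named method, not declared. But the article does name the method, and an analyst who follows it runs tests without covariates. If adjusted contrasts were meant, the same sentence needs correcting.

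Three stronger readings are tempting and are not supported.

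- **That the dose comparisons are biased in general.** Under randomisation the unadjusted difference in change is unbiased over all trials. The shift appears only after selecting trials with a significant imbalance, and the figures above are for the worst pair.
- **That the error rate is badly inflated.** Without the preceding interaction test, the six Bonferroni-corrected t-tests would give about 7% to 13% false positives in triggered trials (n = 14, no true effect), but that is not the planned procedure. With it, the rate is about 3%. Even with one arm different by 1.2 SD, twice the planned d, the excess in triggered trials is 3.8 − 2.2 = 1.6 to 7.2 − 2.4 = 4.8 points. At 5% triggering, that is at most 0.05 × 4.8 = 0.24 points per factor over all trials.
- **That a 0.53 SD shift threatens up to 40% of trials.** The two figures cannot be combined. Five independent factors each with r = 0.5 would explain 5 × 0.25 = 125% of the variance, and ten with r = 0.3 would explain 90%. Many triggering factors would have little link to recovery, and omitting those does little harm.

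It is also fair that separate t-tests avoid pooling variance across all four arms. And the point concerns only the parametric route: the Kruskal-Wallis test planned for non-normal measures carries no covariates either.

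**Conclusion.** The point holds as an inconsistency within section 2.7. When the plan's rule calls for adjustment, the comparisons that answer the dose objectives do not receive it. The consequence is conditional and moderate. In triggered trials with 14 per arm, and an assumed correlation of 0.3 to 0.5 between factor and change, the most unbalanced pair shifts by about 0.32 to 0.53 SD, set against the planned d of 0.6. Requiring a significant interaction limits false claims but does not remove this shift from the estimates. False positives remain about 3% if all arms are equal; among equal arms they reach about 4% to 7% if another arm truly differs by 1.2 SD, against about 2% with adjusted contrasts. The size rests on the assumed correlation, on six pairs and on a single triggering factor. The sample size is not affected. The change is worth making because the affected estimates are the ones on which the trial's dose conclusion rests.

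**What to change.** In section 2.7, replace the separate t-tests with Bonferroni-corrected pairwise contrasts of the T0-to-T1 change, taken from a model with the same covariates as the interaction test. Report the adjusted differences with confidence intervals. Two routes work:

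- an ANCOVA on the T0-to-T1 change with group and the covariates (in SPSS, UNIANOVA with EMMEANS for group, COMPARE and ADJ(BONFERRONI)); or
- explicit time-by-group contrasts in the mixed model.

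EMMEANS with COMPARE applied directly to the mixed model is not enough: it compares groups within a visit or visits within a group, not differences in change between groups.

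The cost is one sentence, with no new data, patients or software. The small downside is that a pooled error term assumes similar residual variance across arms. The change does not alter how covariates are selected, which is a separate matter.
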